### Behavior-change techniques

A wide range of evidence-based behavior-change techniques is used throughout the education and exercise sessions to equip men with the skills to initiate and maintain a healthy lifestyle [40]. These are: (1) goal setting for, and self-monitoring of, weight, physical activity and healthy diet; (2) intention formation with action plans; (3) experiencing exercise sessions with increased challenges as well as positive feedback on exercise achievements and change reinforcement from trainers to build self-efficacy; and (4) identification of barriers and coping planning to help avoid relapse on completion of the program.

### Wait-list controls

The control group will continue with their usual lifestyle for 52 weeks during the trial period but will be offered the RUFIT-NZ program at the end of the 12-month follow-up period.

### Training

All RUFIT-NZ trainers undergo a standardized training session prior to delivering the program. The training is delivered by a member of the RUFIT-NZ investigator team. Trainers receive a standardized booklet outlining the key principles of the program, content details for each of the education sessions, including PowerPoint presentations, participant worksheets and resources to help facilitate group discussions and interactions. Trainers are introduced to the Supportive, Active, Autonomous, Fair, and Enjoyable (SAAFE) delivery principles, which is an evidence-based framework designed to guide the planning, delivery, and evaluation of organized physical activity sessions [41]. Trainers are encouraged to: (1) create a *S*upportive social environment, enabling learning from each other; (2) maximize participants’ opportunities to be physically *A*ctive during the sessions; (3) satisfy participants’ need for *A*utonomy by including elements of choice and providing a rationale for activities; (4) design and deliver experiences that are *F*air by allowing all participants to experience success regardless of their physical abilities; and (5) promote an *E*njoyable experience by focusing on fun and variety and incorporating games where possible.

Nutritionists are provided with a standardized document outlining the key principles to be promoted via RUFIT-NZ and the nutrition topics to be covered in each 1-h session. PowerPoint presentation templates, participant worksheets and resources are also offered to nutritionists to provide the basis for group discussions.

### Baseline demographic information

A self-report web-based questionnaire will be administered at baseline to gather demographic information (age, date of birth, ethnicity, employment status, highest level of education, marital status, and income) from all participants.

### Primary and secondary outcomes

#### Anthropometrics (baseline, 12- and 52-week follow-ups

(1) body weight (measured using calibrated digital scales, (2) waist circumference measured using a tape measure, and (3) height measured using a stadiometer. The primary outcome is defined as the change in body weight from baseline to 52 weeks.

#### Seated systolic and diastolic blood pressure (baseline, 12- and 52-week follow-ups)

Measured using an automated sphygmomanometer (OMRON T9P Intellisense Blood Pressure Monitor) and/or a manual (Reister) Blood Pressure Monitor.

#### Fitness (baseline, 12- and 52-week follow-ups)

Assessed by a 6-km cycle test, a timed sit-to-stand test, and a timed push-up test.

#### Lifestyle behaviors (baseline, 12- and 52-week follow-ups)

Assessed using a self-report questionnaire: (1) leisure time activity (assessed by the Godin Leisure Time Physical Activity Questionnaire) [42]; (2) cigarette smoking (assessed by a smoking history questionnaire) [43]. (3) alcohol intake (assessed by the Alcohol Use Disorders Identification test consumption (AUDIT-C)) [44]; (4) sleep (assessed by the number of hours slept over a 24-h period); and (5) fruit and vegetable intake, discretionary foods, and sugar-sweetened beverage consumption (assessed by the NZ Health Survey questions) [45].

#### Social support and social identity (12- and 52-week follow-ups)

Assessed in a subgroup of participants using a modification of the Athlete Received Support Questionnaire (ARSQ) [46], and social identity measure, respectively [47].

#### RUFIT cost-effectiveness (baseline, 12- and 52-week follow-ups)

Assessed by the EQ-5D [48], a generic and validated measure of choice for which reliable NZ population preference values are available [48–50], to obtain a single preference index for calculation of Quality-Adjusted Life-Years (QALYs).

#### Implementation of RUFIT-NZ as an ongoing program (12- and 52-week follow-ups)

Assessed by an embedded process evaluation conducted using the RE-AIM framework [26, 27]. A mixed-methods (quantitative and qualitative) approach [51] will be used for the process evaluation (see Table 3 for specific details).

**Table 3 Tab3:**
[figure not shown]
Process evaluation conducted using the Reach, Effectiveness, Adoption, Implementation, Maintenance (RE-AIM) metrics

### Data collection and management

All self-reported data are directly input via online surveys to the web-based data capture system Research Electronic Data Capture (REDCap) [52, 53] hosted at the National Institute for Health Innovation (NIHI). All objective data are collected on hardcopy at face-to-face sessions by trained researchers and then input to the same REDCap web-based data capture system hosted and managed at NIHI. At least two measurements are completed for each of the anthropometric and blood pressure measures. Anthropometrics, blood pressure and fitness testing data were collected by trained research assistants. All data are kept for 6 years and will only be used in future studies following a process of participant informed consent.

### Post-trial care

As this is a pragmatic trial, there are no post-trial plans for participants after the 52 weeks. Serious harm is not expected to arise as a result of the intervention. All trainers are required to have a current first-aid certificate and are instructed to report any serious adverse or adverse events related to exercise arising over the 12-week intervention to the central coordinating center. Participants are covered by the Accident Compensation Corporation (New Zealand’s no-fault accidental injury compensation scheme) in the unlikely event that they sustain a physical injury.

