Week 11: Long-term behavior change and overcoming obstacles	• Importance of enjoying PA for long-term maintenance • Overcoming obstacles • Planning for lifestyle change • Relapse prevention	Trainer
Week 12: Team photo and motivational talk	• Wrap-up • Motivational talk • Team photo and certificate	Trainer

*SB* sedentary behavior, *PA* physical activity

Education sessions are delivered predominantly by RUFIT-NZ-trained trainers, with the exception of the nutrition-based components, which are delivered by the club’s nutritionist. RUFIT-NZ trainers are qualified strength and conditioning trainers involved with the respective rugby clubs.

With respect to the group-based in-stadia physical activity sessions, trainers are given the freedom to decide how to structure each of the sessions. This allows the trainers to decide how best to meet the needs of the individual men attending their specific RUFIT-NZ session. Each session progressively increases in difficulty over the 12 weeks, whilst taking account of each individual man’s levels of fitness and is designed to be fun and varied, utilizing the supportive group involvement to foster the sense of being in a “team.” The proposed group size ranges from approximately 15–20 men per trainer. Roll calls are taken at the beginning of each session to assess program attendance.

Throughout the intervention, men are encouraged to follow a daily step-based walking program [34–36]. All participants are encouraged to use a step counter (pedometer or smartphone app) to track their progress and receive a weekly step goal program to follow outside of the structured program. Furthermore, they are encouraged to do other forms of physical activity of their own choosing with a focus on integrating incidental activity into daily life (e.g., parking further from work). The RUFIT-NZ trainers also suggest “homework” physical activity that participants can do outside of the sessions. Participants’ lifestyle behaviors in terms of alcohol, sleep, sedentary behavior, and nutrition will be guided by individual goals, which men set for themselves during the group education sessions and record in a workbook accompanying the program for their own reference.

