### Monitoring and auditing

A data monitoring committee was not deemed necessary due to the low-risk nature of the trial. Data are checked for any values that fall outside the range checks within the REDCap forms by the central coordinating center. An internal audit will be conducted on the trial by a senior project manager independent to the trial.

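### The only adverse event route described is trainer reporting of exercise-related events over the 12-week programme, so harms cannot be compared fairly by randomised arm from it

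*Protocol article*

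**What the plan says.** The protocol article deals with adverse events in one sentence, under Post-trial care. It opens "All trainers are required to have a current first-aid certificate and are instructed to report", and the instruction is to "report any serious adverse or adverse events related to exercise arising over the 12-week intervention to the central coordinating center". It therefore fixes who reports (trainers), what they report (events tied to exercise) and when (the 12-week programme).

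Other sections bear on how far that rule reaches:

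- **Wait-list controls:** "The control group will continue with their usual lifestyle for 52 weeks during the trial period", and these men "will be offered the RUFIT-NZ program at the end of the 12-month follow-up period".
- **Intervention:** activity extends beyond the club sessions. During the programme "men are encouraged to follow a daily step-based walking program", and trainers suggest further exercise to do at home.
- **Fitness, with Data collection and management:** a 6-km cycle test, a sit-to-stand test and a push-up test are done at baseline, 12 and 52 weeks. Trained research assistants collect the results.
- **Primary and secondary outcomes:** "The primary outcome is defined as the change in body weight from baseline to 52 weeks". No adverse event outcome is listed, and the statistical analysis section names no harms comparison.
- **Monitoring and auditing:** "A data monitoring committee was not deemed necessary due to the low-risk nature of the trial".
- **Data collection and management:** "All self-reported data are directly input via online surveys" into REDCap.

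**The concern.** A harms record can be compared between randomised arms only if events are looked for in the same way, over the same period, in both arms. The stated rule does not do this. The reporters are the people who deliver the programme, and only one arm has them. They must also decide whether an event is related to exercise before they report it, and no independent step is described.

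The window is also shorter than the period over which the programme is meant to act. The workshop content includes long-term maintenance of activity and relapse prevention, and effectiveness is judged at 52 weeks. Intended exercise therefore continues after the stated reporting stops.

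What is at stake is the harms record of a programme that is being considered for ongoing delivery to men with a BMI of at least 28. Used alone, this route would give a count of events in one arm with nothing to set it against. The primary weight comparison is not affected.

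**Working it through.** **Inputs.** Sample size: 154 men per arm, 308 in total, 20% loss to follow-up. Intervention: 12-week programme. Primary outcome: 52 weeks. Post-trial care: trainer reporting over the 12-week programme. Wait-list controls: no programme before the end of the 12-month follow-up.

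**The plan's own figure.** The article gives no figure for harms, so the only number to reproduce is the arm size. Per arm, n = 2 × (1.960 + 1.282)² × 12² / 5² ≈ 121.1, rounded up to 122. Dividing by 1 − 0.20 gives 152.5, rounded up to 153, against 154 stated. The arm sizes used below are sound.

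**Time covered by the stated window, with no dropout.**

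| Quantity | Calculation | Result |
|---|---|---|
| Covered person-weeks | 154 × 12 | 1,848 |
| All randomised person-weeks | 308 × 52 | 16,016 |
| Share of all person-weeks | 1,848 / 16,016 | 11.5% |
| Share of intervention-arm time | 12 / 52 | 23% |
| Intervention-arm follow-up outside the window | 40 / 52 | 77% |
| Share of control-arm time | 0 / (154 × 52) | 0% |
| Share of both arms' time within weeks 1–12 | 1,848 / (308 × 12) | 50% |

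**Effect of dropout.** Assume the 20% loss is equal in both arms.

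- If all of it occurs at the start, numerator and denominator shrink together and the share stays at 11.5%.
- If all of it occurs just after week 12, the denominator is 308 × 12 + 0.8 × 308 × 40 = 3,696 + 9,856 = 13,552, and the share is 1,848 / 13,552 = 13.6%.

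The zero for controls does not change in either case.

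**What the percentage means.** It is the share of person-time inside the stated window. It is not the probability that an event is recorded. Inside the window, recording still depends on the trainer learning of the event and judging it related to exercise.

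**Events set against the described route.**

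| Event | Route described? |
|---|---|
| Intervention man, injured in a session | Yes, through the trainer |
| Intervention man, injured walking or exercising at home, weeks 1–12 | Yes, if the trainer hears of it |
| Intervention man, any event in weeks 13–52 | None described |
| Control man, any event in weeks 1–52 | None described |
| Control man, event at a 12- or 52-week fitness test | None described |
| Intervention man, event at the 52-week fitness test | None described |

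**An ambiguity in the wording.** The sentence can be read as limiting serious events to those related to exercise, or as applying that limit to non-serious events only. The two readings give different counts of serious events.

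**The case against.** The strongest reply is that a condensed article is being read as if it were complete. The sentence says what trainers must do; it does not say that nobody else records events. The schedule table, where an adverse event row would most naturally sit, is not shown. Nor are the additional files or the full protocol (version 2.0, 11 April 2019). This part of the reply stands. A reader might infer that the trainer reports are the trial's entire safety record, or that controls certainly have no route. The document supports neither; it supports only that no other route is described.

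A second tempting reading is that injuries outside sessions are lost, so that effective coverage is 12 sessions × 2 hours = 24 hours per man. The text does not support this. The instruction covers any exercise-related event arising over the programme, wherever it happens. Trainers see the men at weekly sessions with roll calls and flag unexplained absences of more than two weeks in a row, and the men join social media groups. Capture outside sessions is unsystematic, not excluded.

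Third, the expectation of no serious harm is a judgement made in advance, not a claim the trial set out to prove. Men are screened with the PAR-Q, and physician consent is needed where an item is endorsed. The decision not to have a monitoring committee, with no interim analysis planned, is a separate matter and does not show that data are missing. No harms objective is declared. All of this is fair, and it limits the weight of the point.

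Finally, self-reported injuries from men who know their allocation may be recalled or reported differently by arm, over up to 52 − 12 = 40 weeks. This is a real cost of the remedy.

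None of these replies gives the stated route a comparator or extends it past week 12.

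**Conclusion.** The point holds as a criticism of the reporting rule that the article states. That rule yields no control-arm reports by construction and nothing for weeks 13–52, and it names no path for events at tests run by research assistants. It also depends on the trainer's awareness and view of causation. A fair between-arm harms comparison cannot be made from it.

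The stated window covers 11.5% of randomised person-weeks with no dropout, or up to 13.6% if the planned 20% loss falls equally in both arms just after week 12. It covers no control time. The conclusion assumes that no other capture exists in the documents not shown. If the full protocol already asks both arms about adverse events at 12 and 52 weeks, what remains is to say so and to resolve the wording on serious events.

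The change is worth making, but it is not critical: the primary result and the sample size are unaffected.

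**What to change.** First check the full protocol. If it has no such item:

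1. Add the same short question to the existing 12- and 52-week REDCap surveys in both arms: any injury or illness needing medical care, or any hospital admission, since the last assessment.
2. Have research assistants record any event at the testing sessions, in the same way in both arms.
3. Tabulate events by randomised arm, regardless of attribution to exercise. Give most weight to hospital admissions and medically attended events, which are less open to selective recall.
4. Keep the trainer reports for rapid notification, and show them separately from the comparison.
5. State whether the exercise-related limit in the trainer instruction applies to serious events.

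**Cost.** One or two survey questions at assessments already scheduled, a brief record at testing sessions and one table. Some unrelated events will be recorded. Recall over up to 40 weeks by unblinded men may be biased, and the report should state that limitation. Recruitment began in January 2019 and 200 men had been randomised by 21 June 2019, so some may already have passed their 12-week survey. For them the 52-week question would have to cover the time since randomisation, with longer recall, in both arms alike.

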### Fidelity

Intervention fidelity is evaluated by means of direct observation by trained research assistants, using a standardized checklist at weeks 4 and 10 of the 12-week intervention. Feedback will be provided by the research team to the trainers to address any gaps in intervention delivery.

### Monitoring and auditing

A data monitoring committee was not deemed necessary due to the low-risk nature of the trial. Data are checked for any values that fall outside the range checks within the REDCap forms by the central coordinating center. An internal audit will be conducted on the trial by a senior project manager independent to the trial.

## Analysis

### Statistical effectiveness analysis

All participants’ data are collected via secure, web-based, case record forms developed by NIHI using REDCap. Statistical analysis will be performed using SAS version 9.4 (SAS Institute Inc., Cary, NC, USA). Baseline characteristics of all randomized participants (including age, ethnicity, employment status, highest level of education, marital status, and income) will be summarized descriptively for intervention and control groups separately. Continuous variables will be presented as means and standard deviations (SD). Categorical variables will be presented as frequencies and percentages. The results will be presented overall and by ethnic group.

Intervention evaluation will be performed on the principle of intention-to-treat (ITT). All statistical tests will be two-sided at a 5% significance level. The primary and secondary outcomes will be first summarized descriptively by randomized group at 12 and/or 52 weeks. The distribution of outcome measures will be checked. The primary outcome at 52 weeks will be evaluated using the analysis of covariance model, adjusting for baseline outcome value and stratification factors. Model-adjusted means and the difference between two groups will be estimated with 95% confidence interval and *p* value. Multiple imputations will be used on missing primary outcome data in the main ITT analysis. Sensitivity analyses using different assumptions on the missing data, including complete case analysis, will also be conducted to test the robustness of the main trial findings. Per-protocol analysis will be performed on randomized participants with no major protocol violations.

Generalized linear regression models will be used to analyze secondary outcomes measured at 12 and/or 52 weeks, using a link function appropriate to the distribution of outcome variable. The regression model will adjust for baseline outcome value (if measured) and stratification factors, similar to the primary analysis. Model-adjusted estimates will be presented with 95% confidence intervals and *p* values. For repeated outcome measures, random-effect mixed models will be used to take into account the correlated data collected from the same participant with a random-subject effect. The consistency of intervention effects between different ethnic groups will be tested using an interaction term between treatment group and ethnicity. As a pre-planned subgroup analysis, separate analyses will also be conducted and presented for the ethnic groups outlined above. Between-subjects’ analysis will compare differences in the mean social identity and social support scores between control- and intervention-group participants at 12 and 52 weeks. Within-subjects’ analysis will also be conducted to compare change in mean scores within groups at 12 and 52 weeks. No interim analysis is planned for the trial. The final trial results will be reported according to the Consolidated Standards of Reporting Trials (CONSORT) 2010 guidelines.

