**Methods:**

A pragmatic, two-arm, multi-center, randomized controlled trial involving 308 overweight and obese men aged 30–65 years, randomized to either an intervention group (*n* = 154) or a wait-list control group (*n* = 154). The intervention-group participated in the 12-week RUFIT-NZ program, a gender-sensitized, healthy lifestyle intervention adapted to the environment and cultural diversity of NZ and delivered through professional rugby clubs. Participants in the intervention group undergo physical training sessions, in addition to workshop-based sessions to learn about nutrition, physical activity, sleep, sedentary behavior, and a range of behavior-change strategies for sustaining a healthier lifestyle. The control group receives the program after 52 weeks. The primary outcome is change in body weight from baseline to 52 weeks. Secondary outcomes include change in body weight at 12 weeks; waist circumference, blood pressure, fitness, and lifestyle behaviors at 12 and 52 weeks; and cost-effectiveness. A process evaluation informed by the RE-AIM framework will evaluate potential implementation of RUFIT-NZ as an ongoing program in NZ after the trial.

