### Sample size

A total of 308 participants (154 per arm) will provide 90% power at 5% significance level (two-sided) to detect a clinically significant 5-kg difference [7] on the primary outcome between the two groups at 52 weeks, assuming a standard deviation (SD) of 12 kg allowing for 20% loss to follow-up. Our SD is conservative and was derived from similar weight management trials for men [25, 33]. Based on the pilot study, the proposed 5-kg difference in body weight would be similar to a reduction in body mass of between 4 and 5% [25]. As the indigenous population in NZ, we aim to recruit a total of 150 Māori participants (~ 50% of the total sample size), which would provide 80% power to detect a 6-kg difference between groups under the same assumptions. Each club will implement strategies to minimize loss to follow-up and improve retention throughout the intervention (i.e., encouraging attendance, trainers notifying the coordinating center if men are absent for more than 2 weeks in a row with no explanation, and social media groups that all the men join) and for the follow-up testing sessions (i.e., provide the men with club merchandise where available, have club players present at the session, and offer alternate session times if required). As part of the consent process, participants are informed that they may withdraw from the program at any time during the study, without providing a reason to the research team or club.

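### For continuous secondary outcomes measured at 12 and 52 weeks, the random-subject mixed model as described is poorly suited to giving a separate effect, with a correct standard error, at each visit

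*Protocol article*

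**What the plan says.** Three statements in the protocol article bear on this.

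- **Outcomes and visits.** The Methods part of the abstract lists as secondary "waist circumference, blood pressure, fitness, and lifestyle behaviors at 12 and 52 weeks", and body weight at 12 weeks only. The outcome sections give the same timing, for example "Lifestyle behaviors (baseline, 12- and 52-week follow-ups").
- **First rule (Statistical effectiveness analysis).** "Generalized linear regression models will be used to analyze secondary outcomes measured at 12 and/or 52 weeks", with a link suited to the distribution. On covariates: "The regression model will adjust for baseline outcome value (if measured) and stratification factors, similar to the primary analysis".
- **Second rule (same section).** Where an outcome is recorded more than once, "random-effect mixed models will be used to take into account the correlated data collected from the same participant with a random-subject effect". No fixed effects are listed for this model, and no residual structure is named beyond the subject effect.

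The primary outcome has its own rule: "The primary outcome at 52 weeks will be evaluated using the analysis of covariance model, adjusting for baseline outcome value and stratification factors". Multiple imputation is planned for missing primary outcome data; none is named for secondary outcomes.

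**The concern.** Waist, blood pressure, fitness and the continuous lifestyle measures fit both rules, and the section does not say which one produces the reported 12- and 52-week estimates. The choice has consequences. A regression at one visit, without imputation, omits men missing at that visit. A likelihood-based mixed model keeps men seen at only one follow-up. The Sample size section allows for 20% loss, so the two models could rest on noticeably different sets of men.

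The mixed model also does not fit the question well as described. The trial wants an effect at the end of the 12-week program and another at 52 weeks. A subject effect with treatment as a single term gives one effect across both visits. If treatment-by-visit is added but the residual variance stays common, each visit's interval is built from the average of the two variances. At stake are the secondary results on whether benefit lasts: they could be blended with the 12-week effect, or carry intervals of the wrong width.

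**Working it through.** **The plan's own figure.** The article gives no figure for the secondary models. Its only related figure is the sample size: "A total of 308 participants (154 per arm) will provide 90% power at 5% significance level (two-sided"), for a 5 kg difference, SD 12 kg and 20% loss. Per arm, 2 × (1.960 + 1.282)² × 12²/5² = 121.05, rounded up to 122. Then 122/0.8 = 152.5, rounded up to 153, or 306 in total against 308 stated. With 154 × 0.8 = 123.2 men per arm, power is 90.5%. The figure reproduces and does not bear on this point.

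**Inputs.** Two follow-up visits with adjusted residual SDs s12 and s52 and within-man covariance c. The significance rule is the plan's: "All statistical tests will be two-sided at a 5% significance level". The documents give neither SD, so r, the larger SD divided by the smaller, is an assumption shown as a range.

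**Reading A: no treatment-by-visit term.** With complete data the model estimates the average of the two visit effects.

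- True variance of a man's two-visit mean: (s12² + s52² + 2c)/4.
- The model uses v = (s12² + s52²)/2 and covariance c, giving (v + c)/2 = (s12² + s52² + 2c)/4.

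The two are identical, so the test is valid even when the SDs differ. Simulation (154 per arm, assumed correlation 0.6, 3,000 runs) gave type I error of 5.1% at r = 1.2 and 4.9% at r = 1.5. With 20% random loss at 52 weeks it gave 5.0% and 4.6%. The shortfall lies in the quantity estimated. If the effect is d at 12 weeks and has gone by 52 weeks, the model estimates (d + 0)/2 = d/2, which describes neither visit.

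**Reading B: treatment-by-visit fitted, one residual variance.** A random-subject effect with one residual variance is compound symmetry. With complete balanced data, both visit contrasts take their standard error from v. Setting the smaller SD to 1:

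- pooled SD = √((1 + r²)/2)
- model SE ÷ true SE = pooled SD at the less variable visit, and pooled SD ÷ r at the more variable visit
- type I error = 2 × [1 − Φ(1.96 × that ratio)]

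| r | Pooled SD | SE ratio, more variable visit | Type I error | SE ratio, less variable visit | Type I error |
|---|---|---|---|---|---|
| 1.0 | 1.000 | 1.000 | 5.0% | 1.000 | 5.0% |
| 1.2 | √1.22 = 1.105 | 0.920 | 7.1% | 1.105 | 3.0% |
| 1.5 | √1.625 = 1.275 | 0.850 | 9.6% | 1.275 | 1.2% |

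A simulation of the pooled-variance interval (123 per arm, correlation 0.6, 20,000 runs) agrees. At r = 1.5, coverage of nominal 95% intervals was 90.3% at the more variable visit and 98.6% at the other. At equal SDs it was 94.8% and 95.0%.

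Readings A and B are alternatives. One fitted model cannot show both faults.

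**The case against.** The strongest reply is that the article says little and the reader supplies the rest. A subject effect does not exclude visit-specific residual variances, and not mentioning treatment-by-visit does not mean it will be left out. Such details commonly sit in a statistical analysis plan, which is not shown here. The two rules can also be read together: plain regression for single-visit outcomes, with a random-subject extension for repeated ones. And per-visit regressions already use each visit's own variance, so they are free of the variance problem.

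Most of this stands, and it rules out several stronger readings that a reader might infer:

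- *The plan forces equal variance.* It names a subject effect; the single residual variance is the usual default and is not stated.
- *The 52-week intervals will be too narrow.* That needs a larger SD at 52 weeks. A wider spread 40 weeks after the program ends is plausible, but the documents give no figure.
- *Each secondary outcome will get two p values.* Nothing says that both models will be fitted to the same outcome.
- *All secondary outcomes are affected.* Body weight is secondary at 12 weeks only. Social support and identity scores have their own described comparison. For categorical outcomes such as smoking status, variance follows the mean and link, so this arithmetic does not carry over.

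What the reply does not remove is that the article states a structure for repeated outcomes, and that the structure suits visit-specific contrasts poorly. The overlap of the two rules would by itself be only a matter of wording.

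**Conclusion.** The point holds as a minor one, for continuous secondary outcomes measured at both follow-ups. Taken literally without the interaction, the mixed model is valid but answers a time-averaged question. With the interaction and a common residual variance, the standard error at the more variable visit is 8–15% too small (type I error 7.1–9.6%). At the other visit it is about 10–27% too large, with the test running at 3.0–1.2%. These sizes rest on an assumed SD ratio of 1.2 to 1.5 and complete, balanced data; at a ratio of 1.0 the error is nil. The primary 52-week analysis of covariance and the sample size are untouched.

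**What to change.** For continuous secondary outcomes measured at both visits, name one repeated-measures model as the source of the reported estimates. It should contain the baseline value, stratification factors, visit, treatment and treatment-by-visit, with an unstructured 2×2 residual covariance in place of the random-subject effect. Read the 12- and 52-week contrasts from it. Keep generalized linear regression for single-visit outcomes such as 12-week body weight.

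The cost is a change of wording and one variance parameter: compound symmetry has two (between-man and residual variance), the unstructured form three (two variances and a covariance). The planned software can fit it and no new data are needed. If the SDs prove equal, almost nothing is lost. Each visit then uses its own variance, and men seen at only one follow-up still contribute.
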